#### 1.1.1. Primary Endpoint

Changes in HbA1c and bodyweight from the beginning of treatment to week 12 after initiation of treatment

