#### 2.6.3. Follow-Up

On the 6th and 12th week, all participants will return to the clinic for an outcome measures assessment. Upon completion of the intervention, participants will be monitored without any intervention for an additional 36 weeks. A final visit to the clinic will be conducted on the 48th week. During these last two visits, a similar assessment on the outcome measures will be carried out to determine the sustainability effect of meal replacement interventions.

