### 2.8. Data Collection and Outcome Measurement

All participants are required to attend the clinic at baseline, 6th, 12th, 24th, 36th, and 48th week for data collection (Table 3).

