#### 2.8.7. Metabolic Profiles

Blood samples of the participants will be collected by a qualified phlebotomist at baseline, on the 12th week and the 48th week. Prior to the day of blood collection, participants will be reminded to fast for eight hours (only plain water is permitted). After that, a total of 7.5 mL of venous blood sample will be taken for biochemical analysis. Blood will be transferred into their respective types of vacutainers and delivered to a certified diagnostic laboratory (Lablink (M) Sdn Bhd, Kuala Lumpur, Malaysia; MS-ISO 15189) for analysis. The results of the blood test will be mailed or given to the participants during the next follow-up. Contact details are provided along with the results to enable the participants to contact the investigators or physician if they have any inquiries. The biochemical parameters measured are listed below:

aHbA1c

Blood samples will be collected in an EDTA tube and measured using an automated high-performance liquid chromatography analyser Adams A1c HA-8180V (Arkray, Tokyo, Japan).

bFasting Blood Glucose

Blood samples will be collected in a sodium fluoride tube and measured using an automated photometric analyser ARCHITECT c16000 and c8000 (Abbott Laboratories, North Chicago, IL, USA).

cFasting Insulin Level

Blood samples will be collected in a serum separator tube, and the fasting insulin level is measured using an automated chemiluminescent analyser (Advia Centaur XP Immunoassay System, Siemens, USA). Insulin resistance index (HOMA-IR) is calculated according to the formula: fasting insulin (micro U/L) × fasting glucose (nmol/L)/22.5 [36].

dLipid Profile Test

Total cholesterol, HDL cholesterol, LDL cholesterol, and total glycerides will be analysed. Blood samples will be collected in a plain tube and measured using an automated photometric analyser ARCHITECT c16000 and c8000 (Abbott Laboratories, USA).

eLiver Profile Test

Total protein, albumin, bilirubin total, Alkaline Phosphatase (ALP), and Alanine Amino Transferase (AST) will be analysed. Blood samples will be collected in a plain tube and measured using an automated photometric analyser ARCHITECT c16000 and c8000 (Abbott Laboratories, USA).

fRenal Profile Test

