### 2.9. Statistical Analysis

Statistical Package for the Social Sciences (SPSS) program version 23.0 will be used to analyse the data. The data will be presented as mean ± SD for parametric data and median (range) for non-parametric data. The normality of data distribution will be tested using the Shapiro–Wilk test. A *p*-value of <0.05 will be used to denote statistical significance. Descriptive analysis including frequencies, percentage, mean, and standard deviation will be used to analyse sociodemographic data and blood pressure.

For the effects of meal replacement on metabolic profiles, anthropometric measurements, satiety levels, hormonal changes, and QoL scores, mixed-design ANOVA will be used to compare between the intervention group and the control group to determine the interaction effect of intervention and time.

To determine the cost-effectiveness, incremental cost-effectiveness ratios (ICER) will be calculated by dividing the difference in total costs (between control and treatment) with the difference in the chosen measure of health outcome or effect (QALY). To assess the sustainability of the meal replacement, mixed-design ANOVA will be used to compare clinical parameters and hormonal level changes between groups on week 12 and week 48.

The main analysis will be conducted in the intention-to-treat (ITT) population in which missing values will be predicted by using the estimating equation method by adapting statistical models to the data observed using the missing-at-random method. Complete case analysis will also be performed in the per-protocol (PP) population.

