The sustainability of the meal replacement formulation to maintain the effect of weight reduction and glycemic control will be assessed by the end of this study through constant monitoring of the participants for another 36 weeks. Possible adverse effects among the participants in the meal replacement trial that we anticipate may occur are nausea or hypoglycemia. The participants will be advised to report any episodes of adverse effects directly to the medical doctor in the research team immediately.

Nevertheless, the commencement of this clinical trial has met with unprecedented challenges due to the COVID-19 pandemic. Most resources and policies have shifted to focus on the management and prevention of the pandemic in the country. As a result, our research progress has been confronted with various restrictions and delays. COVID-19 has led to a restriction of patient visits to clinics for non-essential purposes. Hence, the recruited participants for our study are not permitted to visit the clinic for baseline measurement and intervention.

The European Medicines Association and the US Food and Drug Administration have come out with a series of guidelines and suggestions on conducting clinical trials during the pandemic for better patient protection and to enable continuous trial execution without compromising good clinical practice standards [55,56]. Doherty et al. [57] have reported that one important consensus in handling clinical trials during COVID-19 is reducing the potential COVID-19 exposure risk to patients by minimising hospital visits. Dorsey et al. [57] have suggested that COVID-19 has led to the rise of decentralised studies in which studies may be designed as site-agonistic and flexible in location. Taking the guidelines and approaches from other trials as a reference, we have proposed and outlined a hybrid method for an intervention session that comprises both virtual and physical sessions to mitigate the impact of the delay in the intervention progress [55,56,57,58,59].

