**Output**	
Noncentrality parameter λ	= 8.1087367
Critical F	= 3.9214782
Numerator df	= 1.0000000
Denominator df	= 118
Total sample size	= 120
Actual power	= 0.8063091

**Table 3 ijerph-19-04188-t003:** Data collection Table.

Data Collected/Session	Week 0	Week 6	Week 12	Week 24	Week 36	Week 48
Socio-demography information	/					
Global Physical Activity Questionnaire	/		/	/	/	/
Dietary Assessment						
3-day dietary recall	/	/	/	/	/	/
Food Frequency Questionnaire	/	/	/	/	/	/
Anthropometry Measurements						
Height	/	/	/	/	/	/
Weight	/	/	/	/	/	/
Neck circumference	/	/	/	/	/	/
Waist circumference	/	/	/	/	/	/
Hip circumference	/	/	/	/	/	/
Body composition (muscle mass, fat mass, fat percentage)	/	/	/	/	/	/
Metabolic Profiles						
HbA1c	/		/			/
Fasting Blood Glucose	/		/			/
Insulin Resistance Index (HOMA-IR)	/		/			/
Lipid profile	/		/			/
Renal Profile	/		/			/
Liver Profile	/		/			/
Hormone related to Glycemic Control						
Adiponectin, Leptin	/		/			/
Satiety Measurements						
VAS	/	/	/	/	/	/
Ghrelin, obestatin, peptide YY	/		/		/	/
Quality of life						
ADDQOL-19	/		/	/	/	/
DTSQ	/		/	/	/	/
DDS	/		/	/	/	/
Cost-effectiveness						
EQ-5D-5L	/		/	/	/	/

**Table 4 ijerph-19-04188-t004:** Sociodemographic of participants identified (n = 136).

Parameters	Numbers/Mean
Gender	
Male	81 (59.5%)
Female	55 (40.5%)
Age	54.9 ± 9.3
Race	
Malay	87 (63.97%)
Chinese	25 (18.38%)
Indian	21 (15.44%)
Others	3 (0.02%)
Duration of diagnosis for T2DM (Years)	6.4 ± 4.3
HbA1c Levels (%)	8.5 ± 1.0
Fasting Plasma Glucose (mmol/L)	8.6 ± 2.5

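### The sustainability analysis uses weeks 12 and 48 without naming baseline, so neither of its ANOVA effects directly tests whether the arms still differ at week 48

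*Protocol article*

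**What the plan says.** Sustainability is part of the research objective (section 1.1), and the Discussion (section 4) returns to it: "The sustainability of the meal replacement formulation to maintain the effect of weight reduction and glycemic control will be assessed". The primary endpoint is referenced to baseline and stops at week 12: "Changes in HbA1c and bodyweight from the beginning of treatment to week 12 after initiation of treatment".

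Section 2.9 gives two mixed-design ANOVAs. The first covers metabolic, anthropometric, satiety, hormone and quality-of-life outcomes; its purpose is "to determine the interaction effect of intervention and time", and its time points are not listed. The second is for sustainability: "mixed-design ANOVA will be used to compare clinical parameters and hormonal level changes between groups on week 12 and week 48". It names two visits and not baseline. It does not say whether the group effect or the interaction answers the question, and it does not define a sustained effect.

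On the schedule, sections 2.1, 2.6 and 2.6.3 name visits after baseline at weeks 6, 12 and 48 only; section 2.6.3 says "A final visit to the clinic will be conducted on the 48th week". Section 2.8 says "All participants are required to attend the clinic at baseline, 6th, 12th, 24th, 36th, and 48th week for data collection", and Table 3 agrees with section 2.8. Section 2.8.7 says "Blood samples of the participants will be collected by a qualified phlebotomist at baseline, on the 12th week and the 48th week", while the Table 3 row for "Ghrelin, obestatin, peptide YY" also carries a mark at week 36.

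**The concern.** The clinical question is whether any advantage gained by week 12 is still there at week 48. A two-arm ANOVA with weeks 12 and 48 as its levels offers a group-by-time interaction and a group main effect. The interaction asks whether the arms moved differently after week 12. It is zero if the benefit is kept in full, and equally zero if there never was one. The main effect averages the two visits, so a week-12 difference can carry it even when nothing remains at week 48.

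At stake is one of the trial's stated aims. If a non-significant interaction were reported in support of maintenance, the claim would rest on absence of evidence, from a test with little power against partial loss.

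**Working it through.** **Inputs.** Table 2: effect size f = 0.2055067, alpha 0.05, power 0.80, two groups, four measurements, correlation 0.5. Section 2.2: 120 needed, 156 recruited, up to 30% dropout. Section 2.5: 1:1 allocation.

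**The plan's own figure.** For the between-factors repeated-measures test, lambda = f² × N × m / (1 + (m − 1) × rho) = 0.042233 × 120 × 4 / 2.5 = 8.1087. With 1 and 118 df the critical F is 3.9215 and power 0.8063. This matches Table 2, so the inputs are read correctly. That calculation concerns the between-group effect averaged over visits, not an interaction.

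**Assumptions for the check.** With two equal groups, d = 2f = 2 × 0.2055067 = 0.411 SD, taken as the week-12 benefit. There is no true baseline difference. The correlation between any two visits is 0.5, varied from 0.3 to 0.8. N runs from 109 (156 × 0.7 = 109.2 completers) to 156 (nobody lost).

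**Formulas.** Each effect reduces to a two-sample t test with noncentrality delta × √N / (2 × SD) on N − 2 df.

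- Interaction: week 48 minus week 12, SD = √(2(1 − rho)) = 1.000. Full loss, delta = 0.411: noncentrality 2.15 at N = 109 and 2.57 at N = 156. Half loss, delta = 0.2055: 1.07 and 1.28.
- Group main effect: mean of the two visits, SD = √((1 + rho)/2) = 0.866. If all is lost by week 48, delta = 0.411/2 = 0.2055: noncentrality 1.24 and 1.48.
- Baseline-adjusted week-48 difference: SD = √(1 − rho²) = 0.866. If all is kept, delta = 0.411: noncentrality 2.48 and 2.96.

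**Chance of a significant result, correlation 0.5**

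| Effect tested | Truth at week 48 | N = 109 | N = 120 | N = 156 |
|---|---|---|---|---|
| Interaction | all kept, or never any benefit | 5% | 5% | 5% |
| Interaction | all lost | 57% | 61% | 72% |
| Interaction | half lost | 19% | 20% | 25% |
| Group main effect | all kept | 69% | 73% | 84% |
| Group main effect | all lost | 23% | 25% | 31% |
| Adjusted week-48 difference | all kept | 69% | 73% | 84% |
| Adjusted week-48 difference | all lost, or never any benefit | 5% | 5% | 5% |

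The equal 69/73/84% rows arise because the two SDs coincide at correlation 0.5. Simulation of 20,000 trials per scenario at N = 120 agrees: interaction 61% for full loss and 20% for half loss, main effect 25% for full loss. In the simulation both ANOVA effects are non-significant in 26% of trials if the benefit is kept, 30% if it is lost and 90% if it never existed.

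**Range over correlation (0.3 to 0.8), N = 109 / N = 156.**

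- Interaction, full loss: 0.435 / 0.578 up to 0.920 / 0.981.
- Interaction, half loss: 0.146 / 0.190 up to 0.390 / 0.523.
- Main effect, all lost: 0.261 / 0.353 down to 0.202 / 0.270.
- Adjusted week-48 difference, all kept: 0.606 / 0.762 up to 0.943 / 0.989.

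**Does reading the outcome as change from baseline help?** The sustainability sentence mentions changes for hormones. Subtracting the same baseline value at both visits cancels in week 48 minus week 12, so the interaction is unaltered, and the main effect still averages two visits.

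**The case against.** Four points on the other side carry weight.

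- **A reader might infer that the test cannot tell a lost benefit from a kept one.** That is too strong. Loss is the alternative that the interaction can detect: 57% to 72% power for full loss at correlation 0.5, and 92% to 98% at 0.8. Separation is weak for partial loss, not absent.
- **A reader might infer that absence of any benefit would go unnoticed.** The baseline-to-week-12 primary endpoint addresses that when read alongside, and the group main effect of the same ANOVA helps (73% if kept against 5% if never present, at N = 120). The article simply states no such joint reading.
- **A reader might infer that the protocol intends to call non-significance sustained, or expects rebound.** It says neither. The Introduction and Discussion report rebound in other studies; the trial's own hypothesis in section 4 is maintenance of weight loss.
- **The wording may mean an arm comparison at each week, and the first ANOVA may already include baseline and week 48.** Its time points are not listed, and the four measurements in Table 2 would fit weeks 0, 6, 12 and 48. This is possible but is inference. The sentence that governs sustainability names two visits, and details left to an unseen analysis plan do not change what it says.

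On the schedule, the disputed visits do not enter this analysis: weeks 12 and 48 appear in every version. The week-36 hormone point is also softer than a flat contradiction. Section 2.8.7 concerns metabolic profiles, and section 2.8.8 on hormones gives no timing, so Table 3 may be their only schedule.

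**Conclusion.** The concern holds in a limited form. As written, the sustainability ANOVA has an interaction with the same null for a kept benefit and for none, modest power against full loss, and low power against half loss (19% to 25% at correlation 0.5). Its main effect is significant in 23% to 31% of trials when nothing is left at week 48. Neither effect directly tests the week-48 difference, and the text does not say which decides.

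The sizes rest on a week-12 benefit of 0.411 SD, which comes from an HbA1c effect size, and on the planning correlation of 0.5, which may not describe the interval from week 12 to week 48. A higher correlation makes the interaction more sensitive to loss but leaves its shared null in place.

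The visit schedule is a separate inconsistency with no bearing on these figures.

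**What to change.** In section 2.9, define the sustainability result as the between-arm difference at week 48 adjusted for baseline, with 95% CI, and read it together with the week-12 result. The week-48 contrast distinguishes a kept benefit from the other two cases; the week-12 contrast distinguishes a lost benefit from one that never existed. Report the between-arm difference in change from week 12 to week 48 as an estimate with CI, and state that its non-significance is not evidence of maintenance. The interval matters because a half-kept benefit would be significant at week 48 in only about 25% of trials at N = 120 and correlation 0.5. Testing week 48 only after significance at week 12 is optional.

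Separately, reconcile the visits in sections 2.1, 2.6 and 2.6.3 with those in section 2.8 and Table 3, and clarify whether blood for the satiety hormones is drawn at week 36.

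The cost is analysis wording and a consistency correction. Baseline and week-48 measurements are already planned, so no new data are needed.

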### 2.2. Sample Size

Sample size is calculated using G *Power 3.1 software. The protocol for calculation is as shown below in Table 2. We employed an effect size of 0.2055067, which is obtained from the mean difference value of the HbA1c (%) result in a study by Keogh and Clifton [18]. Based on the calculation, a total of 120 participants is needed for the study. In order to account for up to a 30% dropout, a total of 156 participants will be recruited for this study.

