**Input**	
Effect size f	= 0.2055067
α err prob	= 0.05
Power (1-β err prob)	= 0.80
Number of groups	= 2
Number of measurements	= 4
Corr among rep measures	= 0.5

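### The ITT missing-data rule and the named mixed-design ANOVA do not fit together; if one predicted value fills each gap, the week-12 test is either anti-conservative or diluted

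*Protocol article*

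**What the plan says.** All of the following is in the protocol article.

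- **Missing data (2.9 Statistical Analysis).** The main analysis is in the ITT population, where "missing values will be predicted by using the estimating equation method by adapting statistical models to the data observed using the missing-at-random method". The second analysis is this: "Complete case analysis will also be performed in the per-protocol (PP) population".
- **Test (2.9).** Metabolic and anthropometric outcomes, and so both primary endpoints, are compared by mixed-design ANOVA through the group-by-time interaction. For significance, a p-"value of <0.05 will be used to denote statistical significance".
- **Primary endpoint (1.1.1).** Change in HbA1c and in body weight from baseline to week 12. In Table 3, HbA1c is measured at weeks 0, 12 and 48, and weight at weeks 0, 6, 12, 24, 36 and 48.
- **Dropout (2.2 Sample Size).** "In order to account for up to a 30% dropout", the number recruited is raised from 120 to 156, allocated 1:1.

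The text does not say whether one or several values are predicted per gap, whether arm is a predictor, or how the uncertainty of the predictions enters the test.

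**The concern.** The sentence joins two things that do not normally go together. An estimating-equation method is a way of fitting a model to the data that exist. Predicting missing values is a way of completing a data set. A classical mixed-design ANOVA drops any participant with an incomplete row, so an ITT analysis with that test needs the second. The literal reading is therefore that predicted values are written in and the ANOVA is run on the completed rows.

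If so, predicted participants count as if they had been measured, and the p-values of both primary endpoints are affected. The planned complete-case PP analysis does not repair this. It is a different population, it needs stronger assumptions about who is missing, and agreement with it would not validate the ITT p-value.

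**Working it through.** **1. The protocol's own figure.** Inputs from 2.2 and Table 2: "We employed an effect size of 0.2055067", "Number of measurements = 4", "Corr among rep measures = 0.5", two groups, alpha 0.05, N = 120.

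λ = f² × N × m / (1 + (m − 1)ρ) = 0.2055067² × 120 × 4 / (1 + 3 × 0.5) = 8.1087.

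With 1 and 118 degrees of freedom, the critical F is 3.9215 and power is 0.8063. These reproduce Table 2. The calculation assumes complete data for 120 participants and says nothing about how gaps are handled.

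**2. Inputs for the missing-data check.** 78 per arm (156 / 2); alpha 0.05; within-person correlation ρ = 0.5 (Table 2) and 0.8 (assumed); 10%, 20% and 30% missing at week 12 (30% is the upper allowance in 2.2, the others are assumed). Data are normal with unit variance, and dropout is equal in both arms. With two times, the group-by-time test is the t-test on change, which suits HbA1c up to week 12.

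**3. One prediction per gap, arm in the model: formula.** Let p be the missing fraction. The week-12 residual variance given baseline is a = 1 − ρ². The part of the change explained by baseline has variance b = (1 − ρ)². Per arm, times 1/n:

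- variance that the ANOVA uses: (1 − p)a + b
- actual variance of the arm mean: a/(1 − p) + b

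Type I error ≈ 2 × [1 − Φ(1.96 / √ratio)], where ratio is actual over used.

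Example, ρ = 0.5 and p = 0.3: used 0.7 × 0.75 + 0.25 = 0.775; actual 0.75/0.7 + 0.25 = 1.321; ratio 1.705; 1.96/√1.705 = 1.501; error ≈ 0.133.

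| ρ | Missing | Used | Actual | Ratio | Formula | Simulated |
|---|---|---|---|---|---|---|
| 0.5 | 10% | 0.925 | 1.083 | 1.171 | 0.070 | 0.067 |
| 0.5 | 20% | 0.850 | 1.188 | 1.397 | 0.097 | 0.103 |
| 0.5 | 30% | 0.775 | 1.321 | 1.705 | 0.133 | 0.140 |
| 0.8 | 10% | 0.364 | 0.440 | 1.209 | 0.075 | 0.077 |
| 0.8 | 20% | 0.328 | 0.490 | 1.494 | 0.109 | 0.110 |
| 0.8 | 30% | 0.292 | 0.554 | 1.898 | 0.155 | 0.156 |

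The simulated column comes from 4,000 null trials per row. With dropout depending on baseline (30%, ρ = 0.5), the simulated error is 0.143.

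**4. More time points** (5,000 null trials each, ρ = 0.5, arm in the model). Dropout accumulating to 30% at the last visit gives 0.145 with three times and 0.166 with four. With 30% missing from the second of three times onward it is 0.205. Cumulative 10% and 20% with three times give 0.073 and 0.096.

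**5. Other implementations at 30% missing, two times.**

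| Method | Type I error |
|---|---|
| One prediction plus a random residual, arm in the model | 0.119-0.129 |
| Arm mean filled in | 0.100-0.101 |
| One prediction, arm left out | 0.048-0.054 |
| 20 multiple imputations, Rubin's rules | 0.048-0.052 |
| Complete cases | 0.051-0.056 |

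**6. The price of leaving arm out.** Predicted values then have the same expected change in both arms, so they contribute no difference. The expected estimate is (1 − p) × true effect: 0.9, 0.8 and 0.7 of it at 10%, 20% and 30% missing. A simulation with ρ = 0.5 gave 0.90, 0.80 and 0.70. With arm in the model the estimate was unbiased (ratios 0.995 to 1.003), so there the fault lies in the standard error.

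**The case against.** A reader might infer that the protocol commits itself to treating filled-in values as observed, and that the trial's type I error is therefore well above 5% at the planned dropout. The documents do not support that. They do not say that one value is filled in per gap or that arm is a predictor. The phrase about adapting models to the observed data can even be read as direct model fitting, in which case nothing is filled in and this inflation does not arise. The 30% is an upper allowance for a 48-week study, with no rate stated for week 12. At 10% missing, even the unfavourable method gives only about 0.07.

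A reader might also infer that the method is unweighted generalised estimating equations, which in general need data missing completely at random. The text does not say generalised, and weighted or likelihood-based estimating equations can be valid under missing at random.

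It can further be said that pooling rules and covariance structures belong in an analysis plan that is not shown, and that the complete-case analysis would reveal dependence on the imputation. The first part is fair for such detail. It does not cover a rule that the article states and that conflicts with the test stated beside it. The second part stands only partly: complete cases held their error rate in these simulations, but the planned version is in the PP population.

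**Conclusion.** The concern holds in conditional form. As written, rule and test do not define one analysis, and no handling of imputation uncertainty is stated. If one predicted value per gap goes into the ANOVA, the primary result is harmed either way:

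- arm in the model: type I error of about 0.07, 0.10-0.11 and 0.14-0.16 at 10%, 20% and 30% missing at week 12, and up to about 0.20 with more time points;
- arm left out: error near 0.05, but a true effect diluted roughly in proportion to the missing fraction.

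If the intended method is multiple imputation, or a model fitted directly to the observed data, the inflation is absent. What is then wrong is the sentence and its pairing with the ANOVA.

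The figures assume normal data, equal dropout in the two arms, 78 per arm and a correlation of 0.5 or 0.8. They show what the literal reading would do and are not a prediction of this trial's error rate.

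**What to change.** For the ITT analysis, replace both the missing-data sentence and the ANOVA with one named analysis. Either of these would do:

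- a likelihood-based linear mixed model (SPSS MIXED, REML, unstructured covariance, group-by-time, with the week-12 contrast as the primary test) on all observed data, under missing at random and without filling in values; or
- multiple imputation by arm, with estimates and variances pooled by Rubin's rules.

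A sensitivity analysis that shifts the missing values by a delta is optional.

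The cost is a wording change and modest programming in software already named. Section 3 reports that the intervention had not yet started, so at that stage the rule could be settled before any week-12 data existed.
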